## Abstract

**Objectives::**

To determine the effectiveness of mobile health augmented cardiac rehabilitation (MCard) on health-related quality of life (HRQoL), clinical and behavioural outcomes in post-ACS.

**Methods::**

A single-centre, single-blinded, two-arm randomised controlled trial is planned at Armed Forces Institute of Cardiology (AFIC), Pakistan. The duration was two years, that is from January 2019 till December 2020. A total of 160 participants were recruited and randomly allocated to the control group or the intervention group. Intervention is a mobile health augmented cardiac rehabilitation (MCard), a medically supervised cardiac rehabilitation program for 23-24 weeks. The phase one includes individual counselling during the hospital stay and in phase two includes communication of standardised messages related to healthy lifestyle modification through a specifically designed software.

**Results::**

This clinical trial results will give insight into the impact of MCard in improving the health outcomes (HRQoL, clinical and behavioural) of participants. If proven to be effective, this technology can be scaled up and implemented in other cardiac centres in the country. It utilises fewer human resources and can be delivered at a lower cost.

**Conclusion::**

The study protocol will be giving evidence either MCard can contribute to improving the HRQoL, clinical and behavioural outcomes of post-ACS patients following hospital discharge. Considering the COVID-9 situation, this is the perfect time to implement and evaluate the effectiveness of MCard on health outcomes among post-ACS patients.

## INTRODUCTION

Non-communicable diseases (NCDs) and their risk factors have emerged as one of the major health problems globally.^1^ A significant contributor to NCD mortality is cardiovascular diseases; most notably acute coronary syndrome (ACS).^2^ Cardiovascular disease incidence and mortality are falling in high-income countries. Still, in contrast, they are rising in low and middle-income countries where they now account for nearly half of the disease burden.^3^

ACS has a significant impact on patients’ physical and psychological well-being, contributing to the deterioration of their health-related quality of life (HRQoL). Impaired HRQoL leads to poor health outcomes in the form of morbidity or mortality.^4^ Cardiac rehabilitation has been adopted in the cardiac institute to deal with post-ACS patients’ physical and mental well-being. Many clinical studies^5^,^6^ has proven the effectiveness of cardiac rehabilitation. Still, access, acceptability and affordability to these cardiac rehabilitation programs are limited with overall participation between 20 per cent to 50 per cent only.

Comprehensive cardiac rehabilitation programs as secondary preventive measures involving personalised counselling sessions, behaviour change modification, and empowering patients with self-monitoring devices can reduce the ACS associated with premature mortality, morbidity, and healthcare costs.^7^

Novel ways^8^ are now being explored to improve the provision and uptake of cardiac rehabilitation. Mobile technology provides affordable access to many patients at low cost and without travel and distance constraints. Therefore, there is a growing interest in its potential role in health promotion for modifiable risk factors prevalent in ACS patients.

A clinical trial has been devised to implement a telecommunication based cardiac rehabilitation in which participants will be encouraged for self-care. Suppose this intervention proved to be effective in terms of bringing a change in their HRQoL, behavioural and clinical outcomes, then in coming years. In that case, mhealth technology could be a convenient and effective way of communicating health messages to post-ACS patients in health care settings.

## METHODS

This clinical trial’s study objective is to assess a cardiac rehabilitation program’s effectiveness in which text messages to post-acute coronary syndrome (post-ACS) patients related to healthy lifestyle modification will be communicated. The objectives was as follows:

To determine the effectiveness of MCard on HRQoL outcomes in post-ACS patients.To determine the effectiveness of MCard on clinical outcomes in post-ACS patients.To determine the effectiveness of MCard on behavioural outcomes in post-ACS patients.To determine the acceptability of the MCard among post-ACS patients.

We hypothesised that post-ACS patients who receive the interventions would positively impact their health outcomes (HRQoL, clinical and behavioural) compared to those who receive the usual care. This paper is written per the Standard Protocol Items: Recommendations for Interventional Trials (SPIRIT) 2013 statement. The trial will be registered in line with CONSORT 2010 Statement: updated guidelines for parallel reporting group randomised trials. The detail of participants enrollment with a trial schedule is described through the Table-I and the SPIRIT checklist is attached as supplementary file-1.

**Table-I T1:** Schedule of enrollment, intervention and assessment of recruited participants according to SPIRIT 2013

		Study Period (In weeks)			

	Enrolment	Baseline	Allocation	Post-allocation	
TIMEPOINT		1-2		12	24
***ENROLMENT:***					
Eligibility screen	X				
Informed consent	X				
Empowering with Self-monitoring devices & brochure to fill		X			
Allocation			X		
***INTERVENTIONS:***					
*[Group A]*				⟷	
*[Group B]*				⟷	
***ASSESSMENTS:***					
*Basic Demographic Variables*		X			
HRQoL (MacNew QMLI & SF-12)		X		X	X
*Clinical Outcomes*		X		X	X
*Behavioural Outcomes*		X		X	X
*Adherence*					X

This will be a single-centre, single-blinded, two-arm randomised controlled trial conducted at Armed Forces Institute of Cardiology (AFIC). The clinical trial is registered with the Australian New Zealand Clinical Trials Registry (ANZCTR) under trial identity number ACTRN12619001731189.^9^

The total study duration will be approximately two years from January 2019 till December 2020. After analysing hospital data, it is expected that patient recruitment will take approximately 16-20 weeks (at least 10-12 patients per week) while intervention will take 23-24 weeks.

The patient coming to AFIC emergency and admitted in its wards with ACS diagnosis with ACS will be enrolled in this clinical trial after fulfilling the eligibility criteria as in Table-II. ACS will be diagnosed by at least one on-call cardiologist (cardiac consultant) based on the chest or epigastric pain, radiating to the arm, jaw, neck or back), cardiac markers ((Creatine phosphokinase and/or creatine kinase-MB and/or Troponin I)) and/or electrocardiogram (ST elevation or non-ST elevation).

**Table II T2:** Inclusion and exclusion criteria for MCard

Inclusion criteria	Exclusion criteria
i.Age eligibility: From 35 years till 65 years.	i.Mini-mental State Examination of less than 24.
ii.Gender eligibility: Both	ii.Not physically or mentally capable of handling a mobile phone.
iii.Diagnosed with documented ACS evidence by a cardiologist based on the chest or epigastric pain, radiating to the arm, jaw, neck or back and/or cardiac markers and/or electrocardiogram.	iii.Diagnosed with familial hypercholesterolemia.
iv.Ejection fraction of >25%.	iv.History of cerebrovascular accident.
v.Patients are having mobile phone ownership or a caretaker who can assist in handling mobile.	v.Patient on hemodialysis or peritoneal dialysis.
vi.Patients are giving fully informed voluntary written consent for participation.	vi.A patient diagnosed with hepatitis B or C by serology.
vii.The patient may only have received medical treatment or may have undergone cardiac revascularisation procedure percutaneous coronary intervention or thrombolytic therapy.	vii.Concurrent severe disease, such as malignancy.
	viii.Is or may be pregnant.

The primary outcome measure that is HRQoL physical component summary was used for sample size estimation in STATA version 14. A sample size of 61 per group in a ratio of 1:1 was calculated by two independent mean tests of SF-36 physical component (control group; 39.09 and intervention group 42.65),^10^ assuming SF-36 physical component variability of 6.74 and 7.14 in control and intervention group respectively, a power of 80% and a significance level of 5%. To allow for a predicted 25% drop-out or lost to follow-up rate from adverse events, the sample size has been increased to 80 per group, recruiting 160 participants (80 x 2=160) altogether.

After recruitment into the clinical trial, the baseline information will be recorded by a data collector. The data collector will be blinded to the participant’s actual trial arm before and after the intervention. The random assignment of recruited participants into the two arms was performed by a research associate using web-based permuted block randomisation (4 x 8), ensuring 1:1 ratio between the two arms (i.e. 80 in each). Allocation concealment will be conducted by the sequentially numbered opaque sealed envelope.

The data collector will be communicating with the participants (intervention and control group) for the follow-up data collection at 12 weeks and 24 weeks. Participants will be requested not to disclose their counselling session or text message communication to the data collector. At 12 and 24 weeks, the participants will be asked for a follow-up to the hospital. If the patient cannot come for follow-up, the information will be collected via telephone interview within the ± 01 week period of 12 or 24 weeks.

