### Self-monitoring devices and brochure:

The standard post-ACS care and self-monitoring devices (digital blood pressure machine, digital weight machine and a pedometer) was provided to all patients of both arms to determine the actual impact of health messages communication. All the participants will be briefed on how to use the above three devices. They will be made practically aware of how and when to use these devices**.** Participants will be asked to fill in the brochure their blood pressure and early morning empty stomach body weight once in a week while steps taken shall be recorded daily at the end of the day before they go to sleep.

A trained research associate will assess participants three times during the whole study period that is 23-24 weeks first at baseline before they are discharged from hospital after taking informed written consent. Then at 12 weeks, at the follow-up period and then at 24 weeks post-discharge. In case follow-up is missed or is not undertaken, the telephonic interview will be undertaken. The participant’s demographic questionnaire will be inquired, including information regarding age, gender, educational status, medical history, income per month, the preferred medium of text communication, and behavioural and clinical parameters. At the end of the 24^th^ week, along with other information, the MCard program’s subjective acceptability will also be evaluated on a Likert scale.

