### Primary Outcome is HRQoL:^13^

It is a multidimensional concept that describes individuals or groups’ perceived physical and mental health over some time. The primary outcome changes in HRQoL which will be assessed by validated disease-specific (MacNew quality of life after myocardial infarction (MacNew QLMI) form)^14^ and generic instruments (Short Form 12 (SF-12)).^15^

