Data will be entered and analysed in STATA version 14 using the intention to treat principle. Descriptive data will be presented as frequency and percentages. Continuous data will be presented by means with their 95% confidence intervals. Table and graphs will be constructed for reporting sociodemographic, behavioural and clinical data. Age, gender, education level, comorbidity will be included as potential covariates. All of the analyses will be taken statistically significant at a two-tailed p-value of < 0.05.

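### The 80% power is worked out for physical component scores at one time, while the primary outcome is worded as change in HRQoL; the stated power may or may not apply to change.

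*Protocol article*

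**What the plan says.** The sample-size paragraph (METHODS, after the eligibility table) names the HRQoL physical component summary as the primary measure. It sizes the trial with "two independent mean tests of SF-36 physical component (control group; 39.09 and intervention group 42.65"), "assuming SF-36 physical component variability of 6.74 and 7.14 in control and intervention group respectively, a power of 80" per cent and a 5% significance level. The result is given as "A sample size of 61 per group in a ratio of 1:1 was calculated", raised to 80 per group to allow for 25% loss.

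The section on the primary outcome is worded differently: "The primary outcome changes in HRQoL which will be assessed by validated disease-specific" and generic questionnaires. The section on self-monitoring devices places the assessments "first at baseline before they are discharged from hospital after taking informed written consent", and then at 12 and 24 weeks.

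The analysis paragraph (end of the secondary-outcomes section) gives intention to treat, a short list of potential covariates and the test level: "All of the analyses will be taken statistically significant at a two-tailed p-value of < 0.05". It names no model for the primary outcome. Its covariates are age, gender, education level and comorbidity. The baseline HRQoL score is not listed, but adjustment for it is not ruled out.

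**The concern.** Means of 39.09 and 42.65 are score levels, so 6.74 and 7.14 describe the spread between patients at one time. Change is a different variable. Under randomisation the expected difference between arms is the same for level and change, but the spread need not be. It depends on how strongly a patient's follow-up score tracks the baseline score, and the protocol gives no figure for that.

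Here the baseline is taken during the acute admission and the last score about six months later. A modest correlation is therefore a reasonable possibility, though no figure in the document supports it. If raw change were the variable tested and the correlation were low, a null result would be read against 80% power that the design did not have. The issue does not depend on which questionnaire supplies the score.

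**Working it through.** **Inputs from the protocol.** Means 39.09 and 42.65, SDs 6.74 and 7.14, 61 per group, 80% power and a 5% level (sample-size paragraph); two-sided testing (analysis paragraph). **Assumed, because not given:** the correlation r, and the ratio k of baseline SD to follow-up SD (k = 1 unless stated).

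**Step 1: reproduce the stated size.**
- Difference = 42.65 − 39.09 = 3.56.
- Common SD = √[(6.74² + 7.14²)/2] = √48.20 = 6.94. Standardised difference = 3.56/6.94 = 0.513.
- Normal approximation: n = (6.74² + 7.14²)(1.960 + 0.842)²/3.56² = 59.7, so 60 per group.
- Exact two-sample t-test (noncentral t): 61 per group, power 80.2%.

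The stated 61 is therefore the two-sided t-test on scores at one time, correctly computed.

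**Step 2: unadjusted change, equal SDs.** SD of change = 6.94 × √[2(1 − r)]. Power is by noncentral t with a difference of 3.56.

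| assumed r | SD of change | power, 61 per group | n per group for 80% | power, 80 per group |
|---|---|---|---|---|
| 0.2 | 8.78 | 60% | 97 | 72% |
| 0.3 | 8.21 | 66% | 85 | 78% |
| 0.4 | 7.61 | 73% | 73 | 84% |
| 0.5 | 6.94 | 80% | 61 | 90% |
| 0.6 | 6.21 | 88% | 49 | 95% |

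**Step 3: where the break-even lies.**
- Equal SDs, 61 evaluable per group: r = 0.497. With 60 evaluable (80 less 25%): r = 0.506.
- All 80 per group evaluable: r = 0.338.
- Unequal SDs: the variance of change is s²(1 + k² − 2rk), which equals s² when r = k/2. The break-even is thus 0.4 at k = 0.8 and 0.6 at k = 1.2.

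**Step 4: other analyses of the same data, 61 per group.**
- Follow-up score alone: 80.2% at any r, because r does not enter.
- Follow-up score adjusted for baseline: residual SD = 6.94 × √(1 − r²). At r = 0 this is 6.94 and power is 80%; at r = 0.3 it is 6.62 and power is 84%; at r = 0.5 it is 6.01 and power is 90%.

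**The case against.** The strongest reply is that the protocol never commits to a test of raw change. The analysis paragraph names no primary model, this is a condensed article, and the choice between change, final score and adjusted score is commonly left to an analysis plan that is not shown. The outcome sentence is loose: it names no time point and no subtraction. The secondary-outcomes section also defines clinical outcomes as changes in health and then lists counts such as readmissions. The direction of any error is unknown too, since above r = 0.5 the stated power is conservative.

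Most of this stands, and it limits the point. A reader might infer from the table that the stated power holds only when r is about 0.5 or more, or that the trial is underpowered. The documents support neither reading. The 0.5 threshold belongs to one analysis, an unadjusted comparison of change with equal SDs and 61 evaluable per group, and it moves with each of those conditions. Nor is the size calculation wrong in its arithmetic.

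The inconsistency inside the article remains. The sample-size paragraph describes a score level and the outcome section describes change. An analysis plan could choose a method, but it would not alter what these two sections say.

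**Conclusion.** The mismatch is real and its effect is conditional. The 80% belongs to a comparison of physical component scores at one time. Whether it also belongs to the outcome as worded cannot be told from the document. For unadjusted change at 61 evaluable per group, power runs from 60% to 88% over an assumed r of 0.2 to 0.6, taking equal SDs and the planning difference and SDs at face value. A follow-up-score analysis keeps the stated power at any r, and a baseline-adjusted one keeps or improves it. This calls for aligning two sections, not for a larger trial.

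**What to change.** Make the sample-size paragraph and the primary-outcome section describe the same variable.

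- **Preferred.** Define the primary variable as the physical component score at a stated follow-up time, compared between arms with adjustment for the baseline score. This is the variable that 39.09, 42.65, 6.74 and 7.14 describe. Baseline is already collected, and the adjusted difference still estimates the effect that a comparison of change would target.
- **Otherwise.** Keep unadjusted change, and restate the power in the sample-size paragraph from the SD of change over a stated range of r, with the assumption about baseline and follow-up SDs.

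The first option costs a sentence in the outcome definition and one on the analysis. The second costs a power figure that may be less favourable. Neither requires more patients or more assessments.

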### Intervention Group:

MCard will be a medically supervised cardiac rehabilitation program for a total period of 23-24 weeks for the intervention group. The Phase-I will be initiated during the hospital stay and will include one individual face to face behavioural change modification counselling using HEARTS, a technical package for cardiovascular disease management by the World Health Organization.^11^ Phase-II will be initiated after hospital discharge. The intervention details are devised in line with Tidier guidelines^12^ and are attached as supplementary file 2. The details of the groups are described in Table-III.

**Table III T3:** Detail of the cardiac rehabilitation intervention of the two groups

	Phase I (During hospital stay)			Phase II (After discharge)

	Standard post-ACS care	Empowering with self-monitoring devices	Behaviour change modification counselling	Mobile Text communication
Group A (n=80, control)	√	√		
Group B(n=80, intervention)	√	√	√	√

The core component of the MCard is that the participants will receive the same standardised messages on their mobile phones related to healthy lifestyle modification through a specifically designed software. This will be two-way communication in which the patient will receive text messages and inquire info through texting back. A health professional (principal investigator) and / or an associate researcher will be receiving the calls and messages from the patients and respond to them. The mobile text messages will be the same for all the intervention group. Manually one message per day will be communicated to group B for 23-24 weeks. The principal investigator will communicate a total of 161-168 messages through the MCard designed software. The health messages have been devised by first having a small group discussion with patients to identify the gap in knowledge related to modifiable risk factors (physical inactivity, unhealthy diet, salt intake, tobacco use and medicine defiance). The devised messages were rephrased for communication after having a consultation with a cardiologist. Rephrasing of the messages was conducted for easy understanding of the participants.

### Control Group:

The control group will receive standard care. However, they will not receive text messages on their mobile related to healthy lifestyle modifications.

### Self-monitoring devices and brochure:

The standard post-ACS care and self-monitoring devices (digital blood pressure machine, digital weight machine and a pedometer) was provided to all patients of both arms to determine the actual impact of health messages communication. All the participants will be briefed on how to use the above three devices. They will be made practically aware of how and when to use these devices**.** Participants will be asked to fill in the brochure their blood pressure and early morning empty stomach body weight once in a week while steps taken shall be recorded daily at the end of the day before they go to sleep.

A trained research associate will assess participants three times during the whole study period that is 23-24 weeks first at baseline before they are discharged from hospital after taking informed written consent. Then at 12 weeks, at the follow-up period and then at 24 weeks post-discharge. In case follow-up is missed or is not undertaken, the telephonic interview will be undertaken. The participant’s demographic questionnaire will be inquired, including information regarding age, gender, educational status, medical history, income per month, the preferred medium of text communication, and behavioural and clinical parameters. At the end of the 24^th^ week, along with other information, the MCard program’s subjective acceptability will also be evaluated on a Likert scale.

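### The stated purpose of isolating the text messages does not match the arms: the trial estimates counselling plus two-way texting, on a background of standard care with devices

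*Protocol article*

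**What the plan says.** The protocol article describes the comparison in several places, and the descriptions differ.

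- **Self-monitoring devices and brochure:** standard care and devices "was provided to all patients of both arms to determine the actual impact of health messages communication".
- **Methods, opening aim:** the programme is described by its texts, as one "in which text messages to post-acute coronary syndrome (post-ACS) patients related to healthy lifestyle modification will be communicated".
- **Methods, numbered objectives:** the target is the programme as a whole, for example "To determine the effectiveness of MCard on HRQoL outcomes in post-ACS patients".
- **Methods, hypothesis:** participants who receive the interventions are "compared to those who receive the usual care".
- **Control Group:** "The control group will receive standard care. However, they will not receive text messages on their mobile related to healthy lifestyle modifications". The section mentions neither counselling nor devices.
- **Intervention Group:** phase I includes "one individual face to face behavioural change modification counselling using HEARTS". In phase II, the principal investigator and/or an associate researcher "will be receiving the calls and messages from the patients and respond to them".
- **Table III:** standard care and devices are ticked for both groups; counselling and mobile text communication are ticked for Group B only.
- **Abstract, Results:** "If proven to be effective, this technology can be scaled up and implemented in other cardiac centres in the country", followed by a statement that it needs fewer staff and costs less.

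**The concern.** The purpose clause in the devices section is a claim about what the design can show: because both arms have the same care and devices, the difference between them reveals what the messages do. The opening aim and the Control Group section point the same way, since each characterises the contrast by texts. Table III does not support that claim.

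What is at stake is attribution. If the trial is positive and the report follows the purpose clause, the benefit would be credited to the messages. A centre could then adopt the texts and leave out the individual counselling session, expecting the same result at a low staff cost. Nothing in the trial would support that expectation.

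A second, smaller matter is the label on the comparator. A reader of the hypothesis would take Group A to be ordinary post-ACS care, but that group is equipped and asked to monitor itself.

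**Working it through.** The point rests on the design and not on a figure, so the check compares the components of each arm and asks what one contrast can identify.

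**Step 1. Components by arm** (Table III, with the Intervention Group and devices sections).

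| Component | Group A (n=80) | Group B (n=80) |
|---|---|---|
| Standard post-ACS care | yes | yes |
| Blood pressure monitor, scales, pedometer, briefing, recording brochure | yes | yes |
| One face-to-face counselling session in hospital | no | yes |
| One message per day for 23-24 weeks | no | yes |
| Calls and texts answered by the study team | no | yes |

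**Step 2. The contrast.** Write S for the mean under standard care alone, D for the effect of the devices, C for counselling and M for texting including the two-way contact. Let I(CM) be any interaction between counselling and texting, and I(D) any modification of the package effect by the devices. Then:

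- Mean of A = S + D
- Mean of B = S + D + C + M + I(CM) + I(D)
- B − A = C + M + I(CM) + I(D)

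**Step 3. Messages alone.** To extract M from B − A, one must know C and the interactions. No arm has counselling without texts, and none has texts without counselling. Counselling is assigned to all of Group B and none of Group A, so it coincides exactly with texting. Covariate adjustment cannot separate two factors that never vary independently. Moreover, M already contains live contact with the team, so even M is wider than the standardised messages.

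**Step 4. The package.** B − A is the effect of counselling plus two-way texting when devices are supplied. The abstract's Methods and the Intervention Group section define MCard as those two phases, and the numbered objectives name MCard. For that target the randomised comparison is sound.

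**Step 5. The comparator.** Table III gives devices their own column, apart from standard care, so by the protocol's own classification they are an addition to it. In Step 2 the main effect D cancels. The MCard effect in device-free care would be C + M + I(CM), which equals B − A only if I(D) = 0. No arm is without devices, so the trial cannot test this. The direction of I(D) is also unknown: devices could leave less room for MCard to act, or the messages could work better where patients have the means to monitor themselves. Self-monitoring and pedometer steps are themselves listed as behavioural outcomes, so the background bears directly on some endpoints.

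**Step 6. Sample size.** The planned difference is 42.65 − 39.09 = 3.56 points on the physical component, and it is a difference between whole arms. With SDs 6.74 and 7.14, the pooled value is √((6.74² + 7.14²)/2) = 6.94. At 80% power and two-sided 5%, the normal formula gives 59.7 per group and the t-test version 60.7, which rounds up to the stated 61. Nothing in this point changes that calculation.

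**The case against.** The strongest reply is that the declared target is the package and the design estimates it. The abstract's objective and all four numbered objectives name MCard, MCard is defined as counselling plus messages, and Table III discloses each component by arm. No numbered objective, outcome or sample-size statement is for texts alone. The Control Group section never says that texts are the only difference. The scale-up sentence follows one about the impact of MCard, so the technology it refers to can be read as the whole programme. Giving devices to both arms is a legitimate choice that removes devices as an explanation of any difference.

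Most of this stands, and it limits the point. A reader might infer that the trial cannot reach a conclusion about MCard at all; the documents do not support that, because B − A is the MCard contrast. A reader might also infer that devices in both arms spoil the comparison with usual care. A common device effect cancels, so that inference needs devices to belong to MCard or to modify its effect. The protocol defines MCard without them and gives no evidence of modification. Finally, a reader might want a power figure for the texts alone. That needs an assumed split of the 3.56 points, for which the documents offer no basis.

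What does not fall away is the purpose clause itself. Disclosure in Table III shows that the clause is wrong; it does not make it right. Describing the texts as the programme's core, as the Intervention Group section does, does not make them its only component.

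**Conclusion.** The purpose clause is wrong as written, and the descriptions of the aim and the control arm are incomplete against Table III. The trial validly estimates counselling plus two-way texting added to standard care with self-monitoring devices, versus standard care with the same devices. It cannot estimate the effect of the messages alone. Its result applies to device-free care only on the assumption that devices do not modify the MCard effect.

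No numerical size can be attached: the documents do not say how the expected effect divides between counselling and texting, and they give no information on modification by devices. The conclusion depends only on the allocation of components in Table III. Randomisation, outcomes, sample size and the package comparison are unaffected. Severity is minor to moderate, because the error lies in what may be claimed and not in what is done.

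**What to change.** 1. **Self-monitoring devices and brochure:** delete the purpose clause, or replace it with a statement that devices were given to both arms so that they do not account for a difference between them.
2. **Methods, aim and hypothesis:** state the comparison as in-hospital counselling plus 23-24 weeks of two-way text messaging, added to standard care with self-monitoring devices, versus standard care with the same devices.
3. **Control Group:** say that Group A receives the devices, the briefing and the recording brochure, and receives neither the counselling nor the texts, in line with Table III.
4. **Abstract, Results, and the eventual report:** limit the conclusion and the scale-up statement, including its remarks on staffing and cost, to the package as tested. State that the separate effect of the messages was not estimated, and that application to care without devices assumes no modification by devices.

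The cost is a narrower and less favourable claim. No change to arms, sample size or analysis is needed. Isolating the messages would have required counselling in both arms or a further arm, which is a different trial.
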